# The PANDA study: a randomized phase II study of first-line FOLFOX plus panitumumab versus 5FU plus panitumumab in *RAS* and *BRAF* wild-type elderly metastatic colorectal cancer patients

**DOI:** 10.1186/s12885-018-4001-x

**Published:** 2018-01-25

**Keywords:** Elderly, Metastatic colorectal cancer, RAS, BRAF, Panitumumab, G8, CRASH, Clinical trial

## Abstract

**Background:**

Few data are available regarding the treatment of metastatic colorectal cancer elderly patients with anti-EGFR agents in combination with chemotherapy. FOLFOX plus panitumumab is a standard first-line option for *RAS* wild-type metastatic colorectal cancer. Slight adjustments in chemo-dosage are commonly applied in clinical practice to elderly patients, but those modified schedules have never been prospectively tested. Clinical definition of elderly (≥70 years old) patients that may deserve a more or less intensive combination therapy is still debated. Several geriatric screening tools have been developed to predict survival and risk of toxicity from treatment. Among those, the G8 screening tool has been tested in cancer patients showing the strongest prognostic value for overall survival, while the CRASH score can stratify patients according to an estimated risk of treatment-related toxicities.

**Methods:**

The PANDA study is a prospective, open-label, multicenter, randomized phase II trial of first-line therapy with panitumumab in combination with dose-adjusted FOLFOX or with 5-fluorouracil monotherapy, in previously untreated elderly patients (≥70 years) with *RAS* and *BRAF* wild-type unresectable metastatic colorectal cancer. *RAS* and *BRAF* analyses are centralized. Geriatric assessment by means of G8 and CRASH score is planned at baseline and G8 will be re-evaluated at disease progression. The primary endpoint is duration of progression-free survival in both arms. Secondary endpoints include prospective evaluation of the prognostic role of G8 score and the correlation of CRASH risk categories with toxicity.

**Discussion:**

The PANDA study aims at exploring safety and efficacy of panitumumab in combination with FOLFOX or with 5FU/LV in elderly patients affected by *RAS* and *BRAF* wild-type metastatic colorectal cancer, to identify the most promising treatment strategy in this setting. Additionally, this is the first trial in which the prognostic role of the G8 score will be prospectively evaluated. Results of this study will drive further experimental developments for one or both combinations.

**Trial Registration:**

PANDA is registered at Clinicaltrials.gov: NCT02904031, July 11, 2016. PANDA is registered at EudraCT-No.: 2015–003888-10, September 3, 2015.

## Background

Aging population is highly represented among metastatic colorectal cancer (mCRC) patients [1]. However, the therapeutic decision making in patients older than 70 years of age is still a debated issue due to the paucity of trial-based recommendations.

The clinical definition of elderly (over 70 years) CRC patients that may deserve a more or less intensive combination therapy is still debated. A reasonable approach for defining candidates to different treatment intensity is, in this setting, to consider a cut-off of 75 years old combined with Eastern Cooperative Oncology Group – performance status (ECOG PS) assessment, in order to discriminate patients eligible to combination therapies from patients eligible to less intensive treatment.

In the daily clinical practice, treatment choices are mainly driven by data from retrospective studies, post-hoc or pooled analyses of randomized clinical trials or meta-analyses. However, those results do not necessarily reflect the general mCRC population and are often limited by potential confounding factors [2, 3]. Thus, an individualized treatment approach is usually adopted in this setting, after an in-depth evaluation of biological age, performance status, comorbidities, polypharmacy, social support, global functioning and cognitive abilities, and consequently the risk of experiencing adverse events and decreased quality of life [4].

Currently, in elderly patients, fluoropyrimide-based monotherapy plus bevacizumab, irrespectively of the molecular status of *RAS* (*Rat sarcoma viral oncogene homolog*), is a reasonable upfront treatment based on the result of the phase III open-label AVEX trial. Patients aged ≥70 years were randomized to receive capecitabine with or without bevacizumab. Among 280 randomized patients, the addition of bevacizumab improved progression free survival (PFS), the primary endpoint (9.1 versus 5.1 months; Hazard Ratio (HR) 0.53, 95% Confidence Interval (CI) 0.41–0.69; *p* < 0.0001), as well as the overall response rate (ORR) (19% versus 10%; *p* = 0.04); the difference in overall survival (OS), a secondary end point, was not statistically significant (20.7 months versus 16.8 months; HR 0.79, 95% CI 0.57–1.09; *p* = 0.18) [5].

Data regarding the adoption of a doublet chemotherapy regimen derive from the MRC FOCUS2 and the FFCD 2001–2002 studies [6, 7].

The MRC FOCUS2 was the first randomized clinical trial conducted specifically among elderly and frail untreated mCRC patients, considered unfit for full-dose chemotherapy, with the aim to investigate reduced-dose chemotherapy options. Patients (*n* = 459; 22% < 70 years; 35% 70–75 years, and 43% > 75 years) was randomized to receive treatment with 5-fluorouracil (5-FU)/leucovorin (LV), simplified FOLFOX (folinic-acid, 5-FU, oxaliplatin), capecitabine, or CAPOX/XELOX (capecitabine, oxaliplatin), at 80% of the standard drug doses. The addition of oxaliplatin versus no oxaliplatin resulted in a non-statistically significant trend toward improvement in PFS (median 5.8 versus 4.5 months; HR 0.84, 95% CI: 0.69–1.01, *p* = 0.07), an improvement in overall response rate (ORR: 13% versus 35%; *p* < 0.001) with a lack of benefit in OS. No significant differences in adverse events were observed in patients receiving the combination treatment compared to those receiving a monotherapy. Overall, the MRC FOCUS2 data showed that the addition of reduced-dose oxaliplatin to fluoropyrimidine-based therapy is feasible [6].

The adoption of an irinotecan-based first-line chemotherapy in mCRC patients ≥75 years was evaluated in the phase III FFCD 2001–2002 study. Among 282 randomized patients, those receiving irinotecan plus 5FU/LV showed a significant benefit, over those who received 5-FU/LV alone, in terms of ORR (46.3% versus 27.4%; OR 2.3, 95% CI: 1.4–3.8, *p* = 0.001), a non-significant benefit in terms of PFS (7.3 versus 5.2 months; HR 0.84, 95% CI: 0.66–1.07, *p* = 0.15), and no benefit in terms of OS. Of note, geriatric screening tools were adopted to perform prognostic factor analyses for treatment safety and baseline decrements in cognitive function and Instrumental Activities of Daily Living (IADLs) predicted for grade 3 to 4 toxicity and risk for hospitalization [7].

Epidermal growth factor receptor (EGFR) signalling plays a key role in CRC development and EGFR inhibitors (cetuximab and panitumumab) are well established therapeutic agents in mCRC treatment [8, 9]. From early evidence of a potential subgroup effect in anti-EGFRs activity to post-hoc analyses of randomized trials, *Kirsten rat sarcoma* (*KRAS*) exon 2 and subsequently *KRAS* exons 3 and 4 and *NRAS* exon 2, 3 and 4 mutations have been identified as negative predictive biomarkers for anti-EGFRs activity. Currently, every patient considered for an anti-EGFR therapy must undergo an extended *RAS* mutational testing, including *KRAS* and *NRAS* codons 12, 13 of exon 2; 59, 61 of exon 3; and 117 and 146 of exon 4. Anti-EGFRs treatment is restricted to all *RAS* wild-type patients [10]. However, despite being molecularly selected according to regulatory guidelines, several patients with a *RAS* wild-type mCRC do not benefit from anti-EGFR agents, implying that other mutations/mechanisms of resistance can have an impact on anti-EGFRs activity. *V-Raf murine sarcoma viral oncogene homolog B1* (*BRAF*) V600E mutation is one of these, and available data support the use of *BRAF* as a negative predictive biomarker in clinical practice [11–13].

Although FOLFOX plus panitumumab is a standard first-line therapy option for *RAS* wild-type untreated mCRC patients [14], data on the adoption of anti-EGFRs in elderly mCRC patients are scarce and mostly derived from retrospective or small prospective studies of molecularly unselected patients. Slight adjustments in chemo-dosage are commonly applied in routinely practice to elderly patients, but those modified schedules have never been prospectively tested.

In the subgroup analysis of *RAS* wild-type patients from PRIME study the addition of panitumumab to the first-line FOLFOX-4 showed a benefit over FOLFOX-4 in the subset of patients aged more than 65 years (*n* = 188), in terms of OS (26.6 versus 17.4 months; HR 0.78, 95% CI 0.58–1.09), PFS (9.7 versus 9.2 months; HR 0.88, 95% CI 0.65–1.19) and ORR (49% versus 42%) and did not raise any safety concerns. Although the numbers are small, these data support the fact that there is no evidence of a negative interaction between age and treatment efficacy. The analysis, however, was conducted with an age cut-off of 65 years while the analysis of efficacy in the > 75 years population was limited by patient numbers (*n* = 34) to draw conclusions [15], leaving the question of combined treatment plus panitumumab in properly-defined elderly patients still open.

Similarly, in a small phase II trial, enrolling elderly (age ≥ 70 years) patients considered not candidates for chemotherapy, in the *RAS* wild-type subgroup (*n* = 15), the first-line monotherapy with panitumumab seemed to be effective (overall response rate 13.3%, median PFS: 7.9 months; median OS: 12.3 months) and well-tolerated [16]. Encouraging data were also reported in another study investigating panitumumab monotherapy in molecularly selected *RAS* and *BRAF* wild-type frail elderly patients deemed unfit for chemotherapy or irinotecan-based doublets [17].

It is crucial, thus, to prospectively explore the efficacy of different chemotherapy backbones in combination with panitumumab as first-line treatment in this setting of mCRC patients. Moreover, *RAS* and *BRAF* testing should be definitively proven as clinically useful in frail/very elderly patients, as the addition of anti-EGFRs to chemotherapy could confer a survival advantage and a significant improvement of quality of life in this subgroup of patients.

Several geriatric assessment methods have been developed to help driving treatment choices in elderly patients and to detect disabilities and comorbidities that may potentially contribute to an older patient’s vulnerability predisposing poor outcome and treatment complications. Among them, the G8 screening tool has been tested in cancer patients showing the strongest prognostic value for overall survival [18–20]; the CRASH score is able to stratify patients according an estimated risk of treatment-related toxicities [21].

On the basis of these considerations, we designed the present randomized phase II trial of first-line therapy panitumumab in combination with simplified FOLFOX schedule or with 5-FU/LV alone, in previously untreated elderly patients with *RAS* and *BRAF* wild-type unresectable mCRC.

## Methods/Design

### Aim

The main objective of this trial is to study the efficacy of panitumumab in combination with FOLFOX and with 5-FU/LV in elderly patients with *RAS* and *BRAF* wild-type mCRC.

### Trial design

This is a prospective, open-label, multicenter phase II randomized trial in which initially unresectable and previously untreated *RAS* and *BRAF* wild-type mCRC elderly patients are randomized to receive FOLFOX plus panitumumab for up to 12 cycled followed by panitumumab maintenance until progressive disease (arm A), or 5FU/LV plus panitumumab for up to 12 cycled followed by panitumumab maintenance (arm B) until progressive disease (Fig. 1). A list of participating centers is provided in Table 1.

### Study endpoints

The primary endpoint is Progression Free Survival defined as the time from randomization to the first documentation of objective disease progression or death due to any cause. Documentation of disease progressive disease is defined as per Response Evaluation Criteria in Solid Tumors (RECIST) 1.1 criteria [22] based on investigator assessment.

The secondary endpoints include OS, ORR, early tumor shrinkage (ETS), R0 Resection Rate, overall toxicity rate (OTR), Toxicity Rate and geriatric assessment by G8 and by CRASH.

OS is defined as the time from randomization to the date of death due to any cause. The objective Response Rate will be evaluated according to RECIST 1.1 based on investigator reported measurements.

Early Tumor Shrinkage Rate is defined as the percentage of patients, relative to the total of the enrolled subjects achieving a ≥ 20% decrease in the sum of diameters of RECIST target lesions at week 8 compared to baseline.

Adverse events are evaluated according to the National Cancer Institute Common Terminology Criteria for Adverse Events (NCI CTCAE) version 4.0 [23], during the induction and the maintenance phases of treatment.

Of note, this is the first trial in which the prognostic role of the G8 score will be prospectively evaluated. The assessment by G8 score is defined as the score resulting from the G8 screening tool dichotomizing patients in two groups (score ≤ 14 and > 14). Moreover, the Geriatric Assessment by CRASH score, defined as the identification of four categories of different toxicity risk (low, medium-low, medium-high, high), will be prospectively correlated with toxicity.

### Clinical setting

Metastatic colorectal cancer patients aged ≥70 years are evaluable for the inclusion in the present study, an ECOG PS of 1 or 2 is required for patients aged 70 to 75 years, while an ECOG PS of 0 to 1 is required for patients aged more than 75 years.

Main eligibility criteria include:measurable disease according to RECIST version 1.1;centrally assessed wild-type *RAS* and *BRAF* status of primary colorectal cancer or related metastasis *(see following paragraph);*geriatric assessment by G8 screening tool and CRASH score *(see following paragraph)*;adequate bone marrow, liver, and renal function;no previous exposure to an oxaliplatin-containing adjuvant therapy. Previous adjuvant chemotherapy with fluoropyrimidines alone is allowed if more than 6 months have elapsed between the end of the adjuvant therapy and disease relapse.

Main exclusion criteria include:peripheral neuropathy of grade 1 or higher according to NCI CTCAE version 4.0;contraindications to study drugs.

Each patient’s eligibility is verified by using an electronic WEB-based system.

### Molecular assessment

Molecular testing of *RAS* and *BRAF* mutational status on tumor specimen for each patient is performed as a screening procedure and centralized at the Department of Surgical, Medical, Molecular Pathology and Critical Area, University of Pisa and Unit of Immunology and of Oncological Molecular Diagnostics, Department of Oncological Diagnostics, Oncology Institute of Veneto – IRCCS, Padova, Italy.

*KRAS* codon 12, 13, 59, 61, 117 and 146 mutations, *NRAS* codon 12, 13, 59, 61, 117 and 146 mutations and BRAF V600E mutation will be assessed by means of MALDI-TOF MassArray (Sequenom®).

### Geriatric assessment

Geriatric assessment by G8 screening tool is performed at baseline and at the time of disease progression. The G8 screening tool includes seven questions focusing on nutritional status, mobility, neuropsychological problems, medication use, self-rated health status and age. Each question provides from 2 to 4 possible answers and a score is assigned at any type of answer. The sum of the answers scores plus a score based on the age of the patient will be the final score. It ranges from 0 to 17 (Table 2).

**Table 2 Tab2:** G8 Screening Tool

	Items	Possible Answers
A	Has food intake declined over the past 3 months due to loss of appetite, digestive problems, chewing or swallowing difficulties?	0: severe reduction in food intake 1: moderate reduction in food intake 2: normal food intake
B	Weight loss during the last 3 months?	0: weight loss > 3 kg 1: does not know 2: weight loss between 1 and 3 kg 3: no weight loss
C	Mobility	0: bed or chair bound 1: able to get out of bed/chair but does not go out 2: goes out
D	Neuropsychological problems	0: severe dementia or depression 1: mild dementia or depression 2: no psychological problems
F	Body Mass Index (weight in kg/height in m2)	0: BMI less than 19 1: BMI 19 to less than 21 2: BMI 21 to less than 23 3: BMI 23 or greater
G	Takes more than 3 medications per day	0: yes 1: no
H	In comparison with other people of the same age, how does the patient consider his/her health status?	0: not as good 0,5: does not know 1: as good 2: better
I	Age	0: > 85 1: 80–85 2: < 80

The CRASH screening tool is performed only at baseline by local investigators according to the online CRASH Score Calculator developed by Moffit Cancer Center [24]. This score stratifies patients in four risk categories of severe hematologic, non-hematologic and combined toxicities.

The hematologic sub-score is calculated by the sum of scores (ranged from 0 to 2) assigned to the following items: diastolic blood pressure, IADL, LDH, and MAX2 index.

The non-hematologic score is calculated by the sum of scores (ranged from 0 to 2) assigned to the following items: ECOG PS, Mini Mental State Exam (MMSE), Mini Nutritional Assessment and MAX2 index.

The combined score is calculated by the sum of scores (ranged from 0 to 2) assigned to the following items: diastolic blood pressure, IADL, LDH, ECOG PS, MMSE, MNA and MAX2 index (Table 3).

**Table 3 Tab3:** CRASH Scoring System

Item	Score
Diastolic Blood Pressure	0: ≤72 mmHg 1: > 72 mmHg
IADL	0 = 8 1: < 8
LDH	0: ≤ 0.74 x ULN 2: > 0.74 x ULN
ECOG PS	0: 0 1: 1–2 2: 3–4
MMS	0: 30; 2: < 30
MNA	0: 28–30 2: < 28
Chemotherapy risk (MAX2)	0: arm B (FU/LV + Pani) 1: arm A (FOLFOX+Pani)

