### Statistical design

Assuming exponentially distributed event times, uniform accrual over time, no loss to follow-up and an expected median PFS time equal to or greater than 9.65 months with both experimental regimens, corresponding to a 6-month PFS probability ≥65%, a sample size of 90 patients in each arm will guarantee to the study a power equal to 90% for a one-sided Brookmeyer-Crowley test, with a type I error rate equal to 5%, against the null of a median PFS time equal to or less than 6 months.

The Kaplan-Meier approach will be used to estimate median PFS for each treatment arm. The hypothesis test will be conducted according to Brookmeyer-Crowley, comparing the cumulative hazard estimate at 6 months to the –log(0.50). No formal comparison between the results of the two treatment arms will be allowed.

All analyses of secondary endpoints will be descriptive only and no formal statistical comparisons will be made between the arms. Survival curves will be calculated according to Kaplan–Meier methods. Log-rank tests stratified by the same factors as used for randomization will also be performed, as well as multivariable models including all the significant baseline variables. The median event times and corresponding 2-sided 95% CI for the median will be provided.

The prognostic value of baseline G8 assessment for predicting patients’ outcome will be investigated through Cox proportional hazards model. The relationship between baseline data and patients’ survival will be graphically investigated. The prognostic value of changes of G8 score from baseline to disease progression will be similarly investigated. The analyses will be adjusted for known clinical prognostic factors. All analyses will be adjusted for multiple testing.

The association of G8 score with clinical outcome will be assessed in terms of the difference in OS in the two groups of patients (score ≤ 14 versus > 14) by means of log-rank test.

The association of CRASH score with toxicity will be assessed comparing G3–4 adverse events in the four risk categories (low, medium-low, medium-high and high risk) by means of chi-square test.

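### The randomised arm is an item of the CRASH score, so a single chi-square of CRASH category against G3–4 toxicity mixes a treatment effect with geriatric prediction

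*Protocol article*

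**What the plan says.** The protocol article (Geriatric assessment) builds three CRASH scores from Table 3:

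- hematologic: "diastolic blood pressure, IADL, LDH, and MAX2 index"
- non-hematologic: "ECOG PS, Mini Mental State Exam (MMSE), Mini Nutritional Assessment and MAX2 index"
- combined: "diastolic blood pressure, IADL, LDH, ECOG PS, MMSE, MNA and MAX2 index"

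MAX2 is in all three. Table 3 labels it chemotherapy risk and assigns it entirely by treatment arm: "0: arm B (FU/LV + Pani) 1: arm A (FOLFOX+Pani").

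The Statistical design section plans the analysis as "comparing G3–4 adverse events in the four risk categories (low, medium-low, medium-high and high risk) by means of chi-square test". Treatment arm is not mentioned there. The sentence on adjusting for known prognostic factors belongs to the G8 paragraph, and the CRASH paragraph has no counterpart. The same section calls all secondary analyses descriptive and rules out formal comparisons between the arms.

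On timing, "The CRASH screening tool is performed only at baseline by local investigators", and the eligibility list in Clinical setting includes "geriatric assessment by G8 screening tool and CRASH score".

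**The concern.** Every arm A patient carries one more CRASH point than an arm B patient with the same geriatric findings. Those near a category boundary are moved up a category by the allocation alone. If the arms also differ in G3–4 toxicity, the higher categories hold more of the more toxic arm. Toxicity then rises with CRASH category even if no geriatric item predicts anything.

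What is at stake is the meaning of a positive result. The Discussion hopes for evidence that would support these tools in everyday treatment of older patients. For that purpose one needs to know whether the patient items carry information. A test that does not separate the arms cannot show this. It also lets part of an arm comparison into an analysis set in which such comparisons were ruled out.

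**Working it through.** The article states no power, error rate or expected effect for the CRASH test, so there is no figure of its own to reproduce.

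**Inputs from the article.** 90 patients per arm, 180 in total, allocated 1:1. Table 3 points: diastolic pressure 0/1, IADL 0/1, LDH 0/2, ECOG PS 0/1/2, MMS 0/2, MNA 0/2, MAX2 0/1. Clinical setting allows PS up to 2, so ECOG adds at most 1.

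**Attainable maximum, arm A against arm B.**

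- Hematologic: 1+1+2+1 = 5 against 4.
- Non-hematologic: 1+2+2+1 = 6 against 5.
- Combined: 1+1+2+1+2+2+1 = 10 against 9.

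The top value of each score can be reached only in arm A.

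**Assumptions, because the article gives none.** G3–4 rates of 40% in arm B and 60% or 70% in arm A; independent items, each positive in 50%; illustrative cut-points. Toxicity depends on arm only.

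**Worked case: hematologic score, categories 0–1, 2–3, 4, 5.** Without MAX2 the score takes the values 0, 1, 2, 3, 4 with probabilities 0.125, 0.25, 0.25, 0.25, 0.125. Adding one point in arm A gives:

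| Category | Arm B | Arm A | Toxicity at 40% v 60% |
|---|---|---|---|
| 0–1 | 0.375 | 0.125 | (0.375×0.4 + 0.125×0.6)/0.5 = 45% |
| 2–3 | 0.500 | 0.500 | 50% |
| 4 | 0.125 | 0.250 | (0.125×0.4 + 0.25×0.6)/0.375 = 53.3% |
| 5 | 0 | 0.125 | 60% |

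A clean gradient from 45% to 60% appears with no geriatric effect. The pooled category weights are 0.25, 0.5, 0.1875 and 0.0625, and the overall rate is 0.5. The chi-square noncentrality is n × Σ w(p − 0.5)² / (0.5×0.5) = 180 × (0.25×0.05² + 0.1875×0.0333² + 0.0625×0.10²)/0.25 = 1.05. On 3 degrees of freedom the nominal 5% test then rejects in about 12%. At 40% v 70% the category rates are 47.5%, 55%, 60% and 70%, the noncentrality is 2.39, and rejection is about 22%.

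**Simulations**, 2,000 to 3,000 trials per setting, with item prevalences of 40–70% and two sets of cut-points per score. Share of trials in which the nominal 5% test rejects:

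| Arm B v arm A | Combined score | Sub-scores | Arm-stratified test |
|---|---|---|---|
| Equal rates (50% v 50%) | 4–5% | 4–6% | 4–5% |
| 40% v 60% | 6–8% | 8–14% | 4–6% |
| 40% v 70% | 9–11% | 11–30% | 4–6% |

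For scale, a direct comparison of the arms at 40% v 60% with 90 per arm has 77% power. Only a small part of an arm effect passes through to the combined category, and more of it to the sub-scores.

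**The case against.** **Chemotherapy risk belongs to CRASH.** As the article describes it, the score includes chemotherapy risk, so asking whether the complete score tracks toxicity is legitimate. The arm is a component of the exposure, not an outside confounder. This stands. What the test cannot do is credit the geriatric items.

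**The effect may be small.** The inflation for the combined score is modest, and the plan does not say which of the three scores is tested. The assumed gaps of 20–30 percentage points have no source in the article. The reduced-dose trial in elderly and frail patients cited in the Background found no significant difference in adverse events when oxaliplatin was added. This leaves the size uncertain. It does not remove the structure: Table 3 itself ranks arm A as the higher chemotherapy risk.

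**Arms may be separated elsewhere.** An analysis plan that is not shown may stratify, so a test pooled over the arms is partly a reading of silence. That is fair. Still, the method stated is one chi-square over four categories, and a stratified analysis would be a different one.

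**The analyses are descriptive.** This limits the consequences. It does not cure the mixing, because a descriptive table shows the same artificial gradient.

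**Stronger readings the article does not support.** A reader might infer that the test can succeed only because oxaliplatin adds toxicity, or that its result would say nothing. Neither follows, since the other six items can also drive it. A reader might also infer an eligibility failure, because the Table 3 score cannot be completed before the arm is known. But the article sets no CRASH threshold for entry. The patient items can be collected at baseline and MAX2 filled in after allocation, so no entry decision depends on it.

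**Conclusion.** The point holds as an attribution problem in a secondary analysis. The arm supplies 1 of 5, 1 of 6 or 1 of 10 attainable CRASH points, and the stated test does not separate the arms. A positive result may therefore come partly or merely from a treatment difference in toxicity.

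If the arms differ by 20 to 30 percentage points in G3–4 toxicity and no geriatric item matters, the nominal 5% test rejects in about 6–11% for the combined score and about 8–30% for the sub-scores. These figures rest on assumed toxicity rates, item prevalences, independence of items and cut-points. If the arms have equal toxicity, the error rate stays nominal. That the arm enters the score rests on Table 3 alone and needs no assumption.

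This should be fixed. The primary progression-free survival test, the sample size and the randomisation strata are unaffected.

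**What to change.** In Statistical design, replace the single chi-square by a test of CRASH category against G3–4 events stratified by arm. Suitable choices are Cochran–Mantel–Haenszel, a Mantel trend test across the ordered categories, or logistic regression with arm and CRASH as terms. Report the CRASH–toxicity table within each arm. Within an arm MAX2 is constant, so any remaining association comes from the patient items. Stratifying in this way is not a comparison of the arms and respects the rule against such comparisons.

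The full CRASH score and its categories can be kept. A score without MAX2 is an optional sensitivity analysis; its drawback is that the category cut-points do not apply to it.

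The cost is a change of analysis wording and one extra table layout. No new data are needed.
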